**Objectives: see grant application form.**

## **2.2 APPROACHES, HYPOTHESES AND CHOICE OF METHOD**

### **2.2.1 Study design**

We propose a factorial (2x2), multi-center, assessor-blind pragmatic RCT to evaluate the longitudinal effect of MT in NICU and/or after discharge on premature infants and their primary caregivers across a 12-month time period (Fig. 1). The factorial design will allow testing the independent effect of each combination: NICU-MT, post-discharge MT, both, or neither, as well as interactions between them. Participants will initially be recruited from the NICU of participating hospitals according to the following in- and exclusion criteria:

- (1) Infants: Born below 35 weeks GA, of both genders, any ethnicity, from single or multiple pregnancies, who have achieved sufficient medical stability (as determined by medical staff) to start MT.
- (2) Primary caregivers: One of the parents/caregivers must provide written, informed consent before any study procedures occur. Primary caregivers should agree to engage in at least 2 of the 3 MT sessions per week during NICU, and/or in 5 of the 7 MT post-discharge sessions. To ensure feasibility, primary caregivers should live within reasonable commuting distance from the treating NICU in order to be eligible for participation.

The 2x2 factorial design entails a two-phase protocol covering both the stay in the NICU and municipal care after discharge from hospital. During NICU stay, participants will be randomly allocated to receive either MT integrated in standard NICU care or standard NICU care alone. Before discharge to home, participants will again be randomly allocated to either MT integrated in municipal care or standard municipal care. Standard care may include other early intervention methods of care with the exception of other music-based approaches. Treatment fidelity (adherence and competence) will be evaluated by independent raters using video recordings.

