#### **Secondary outcomes:**

(1) **Infant development** will be assessed blindly using the Bayley Scales of Infant and Toddler Development (BSID). It covers cognitive, language, and motor development and is considered the gold standard for assessing development of young and premature infants up to 42 months [37].

(2) **Re-hospitalization** during the first year of life (excluding outpatient visits), based on electronic health records: Safely bonded parents panic less when an infant develops fever and may be more capable of

handling minor illnesses of their infants. A previous study [29] found a promising difference of 15% with music therapy compared to 30% with standard care.

(3) Infant *socio-emotional development* will be evaluated using the Ages and Stages Questionnaire Social-Emotional (ASQ:SE). This is a parent-completed questionnaire that targets social-emotional competence and problem behaviours, with 19 to 22 Likert-scaled items depending on child age [38, 39].

(4) Infant *social behaviour* will be assessed using the Alarm Distress Baby Scale (ADBB) [40]. It covers facial expression, eye contact, general level of activity, self-stimulating gestures, vocalizations, response to stimulation, relationship. It has shown high sensitivity, specificity and reliability [40].

(5) *Parental depression* will be assessed with the Edinburgh Postnatal Depression Scale (EPDS). The 10-item self-report instrument assesses caregiver's postpartum depressive symptoms, focusing specifically on more severe problems rather than those that are common to nearly all new mothers (such as loss of energy, feeling tired, changes in appetite and sexual drive). It has shown high sensitivity and specificity in two Norwegian studies [41, 42].

(6) Level of parental stress will be assessed with the Parental Stress Scale (PSS). This is a self-report 18-item questionnaire that assesses *stress levels associated with parenting* [43].

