(7) In addition, a checklist of *medical and social factors* will be completed at baseline and updated 1-2 days prior to discharge, to track the presence of particular factors that might impact infant responsiveness (e.g., intraventricular hemorrhage, presence and nature of sedation, abnormal hearing screening at discharge, etc.), or parental engagement (e.g., socioeconomic status, receiving treatment for mental health or substance use problems, etc.). Within the MT group, physiological signs (heart rate, respiratory rate and oxygen saturation) and behavior state will be informally monitored during the course of MT as part of the provision of infant-directed approaches. This part will also assess use and costs of medical services. Existing electronic health records will be used wherever possible to improve reliability and completeness and to reduce costs and burdens of data collection.

**Cost-effectiveness:** We will collect the data that are necessary for analyzing cost-effectiveness both from a health services perspective (i.e. costs of all treatments incurred within the health sector) and from the broader societal perspective (i.e. including also indirect costs such as productivity losses). If clinical effectiveness is found, we will apply for separate funding to analyze incremental cost-effectiveness ratios and willingness to pay. Otherwise, these data will be used to describe the context in which the treatment took place.

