#### **2.2.4 Trial procedures, statistical considerations, and data management**

**Randomization, allocation concealment and blinding:** After informed consent and baseline assessment, participants will be randomly assigned to NICU-MT or standard care using a computer-generated randomization list, with ratio 1:1, in blocks with sizes of 2 or 4 varying randomly, using email and an online system. The random allocation sequence will be generated and administered by people with no involvement in the clinical work to ensure allocation concealment. One day before discharge to home, participants will be randomized a second time to post-discharge MT or standard care in a 1:1 ratio, using the same procedures. This two-step randomization was chosen as the best way to create balance among those remaining in the study for the aftercare phase, and to avoid differential drop-out in the NICU phase due to expectations for the aftercare phase. In multiple pregnancies, only the first-born infant will be included and randomized, while remaining siblings will receive the same interventions for ethical and practical reasons. Blinding of interventions is not possible, but all outcomes that are not self-reports will be blinded, and success of blinding will be tested.

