where  $PBQ_{it}$  denotes the PBQ score for participant  $i$  at measurement  $t$ ,  $time_t$  the time from baseline at measurement  $t$  and  $gr_i$  the randomization group of participant  $i$ .  $\beta_0$ ,  $\beta_1$ ,  $\beta_2$  and  $\beta_{12}$  are the coefficients estimated in the model,  $U_i$  is an individual random term per participant and  $\varepsilon_{it}$  an independent, identically distributed error term. In the second step we refine the model to take into account both randomization steps, leading to the extended model:

$$PBQ_{it} = \beta_0 + \beta_1 time_t + \beta_2 grR1_i + \beta_{12} time_t grR1_i + \beta_3 grR2_i + \beta_{13} time_t grR2_i + U + \varepsilon_{it} ,$$

with the same notation as above and  $grR1_i$  and  $grR2_i$  denoting the groups from the first and second randomization, respectively. In these models  $\beta_1$  describes a group-independent time effect,  $\beta_2$  and  $\beta_3$  a time-independent group effect, and  $\beta_{12}$  and  $\beta_{13}$  the time-dependent change of the group effect. We will investigate both linear and simple contrasts (comparing each time point with the baseline) in time to assess the treatment effect. The same analyses will be done for the secondary outcomes; using an analogous generalized linear mixed model for binary outcomes. Per-protocol analyses will include those who received at least 6 MT sessions in the NICU and at least 5 MT sessions post-discharge, respectively; these are considered the minimum numbers for the intervention to be successful. Additionally, we will conduct exploratory statistical analyses for prespecified subgroups (sex; GA at birth [ $<28$  wks, 28 to  $<32$  wks, 32 to  $<35$  wks]; hearing status at discharge [normal vs. abnormal]; bonding at baseline [PBQ impaired bonding score  $\geq 11$  vs.  $<11$ ]) as well as qualitative/mixed-methods analyses of process data to maximize learning.

**Data management plan:** To promote transparency and applicability of trial results and to facilitate re-analysis by other researchers while also protecting anonymity, de-identified individual patient data will be made available through the Norwegian Centre for Research Data (NSD).

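### Gestational age at birth is recorded for every infant but enters no infant-outcome model, so precision is probably lost on Bayley, ADBB, ASQ:SE and re-hospitalization

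*Combined protocol and SAP*

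**What the plan says.** Section 2.2.4 (Data analyses) names two-group tests and linear mixed models for the PBQ. The first model has time, first-randomization group and their interaction. The extended model adds the second group and its time interaction, with the two indicators "denoting the groups from the first and second randomization, respectively". Each model has a random participant term; no other term is listed. The rule for everything else is: "The same analyses will be done for the secondary outcomes; using an analogous generalized linear mixed model for binary outcomes".

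GA appears in two relevant places. In section 2.2.1 it is an eligibility criterion: "Born below 35 weeks GA, of both genders". In section 2.2.4 it defines one of the "exploratory statistical analyses for prespecified subgroups (sex; GA at birth", in three bands (below 28, 28 to under 32, and 32 to under 35 weeks).

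Allocation is "with ratio 1:1, in blocks with sizes of 2 or 4 varying randomly"; no stratification by GA is stated. The amendment tables do not alter any of this.

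The secondary outcomes in section 2.2.3 include infant development, which "will be assessed blindly using the Bayley Scales of Infant and Toddler Development (BSID", as well as ADBB, ASQ:SE and re-hospitalization in the first year. The same section provides for a medical and social checklist "to track the presence of particular factors that might impact infant responsiveness", so the plan itself expects infant condition at entry to matter.

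**The concern.** The trial deliberately pools infants across a wide range of maturity. The PBQ is measured at baseline, so its contrasts draw on each parent's starting value. Re-hospitalization has no pre-randomization value by definition, and a developmental test can hardly have a useful one in an infant still in the NICU. For these outcomes nothing about prognosis enters the comparison as the models are written. Any part of the outcome spread that GA explains stays in the error term. Neither the randomization nor the analysis deals with it, although the variable is already in the data set.

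At stake is efficiency on the outcomes that serve secondary objective 2 (infant development and social behaviour) and on re-hospitalization.

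**Working it through.** **Step 1. The plan's own figure, for reference.** Inputs from section 2.2.4: difference 4, SD 8, two-sided alpha 0.025, power 80%.

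- n per arm = 2 × (2.241 + 0.842)² × (8/4)² = 76.0, rounded up to 77, so 154 in total. A noncentral-t calculation gives 80.1% power at 155. The stated 155 reproduces.
- Clustering: 155 × (1 + 30 × 0.01) = 201.5 with 31 per country, or 155 × (1 + 31 × 0.01) = 203.05 with 32. The stated 203 reproduces.
- Attrition: 203 / 0.8 = 254, against a target of 250; 250 × 0.8 = 200 analysed.

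This chain concerns the PBQ and does not involve GA. It supplies the 200 used below.

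**Step 2. Continuous outcome measured once.** Let R² be the share of outcome variance explained by GA. The documents give no value, so R² is an assumption, shown as a range.

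- SE ratio (adjusted / unadjusted) = √(1 − R²).
- Equivalent gain in infants = 1/(1 − R²) − 1.
- Power = Φ(d / (√(1 − R²) × √(4/200)) − 2.241), for an illustrative d = 0.4 SD at alpha 0.025, with no clustering allowance. The plan sets neither this d nor this alpha for infant outcomes.

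| R² (assumed) | SE ratio | Equivalent extra infants | On 200 analysed | Power at d = 0.4 |
|---|---|---|---|---|
| 0 | 1.000 | 0% | 0 | 72.1% |
| 0.02 | 0.990 | 2% | about 4 | 73.1% |
| 0.05 | 0.975 | 5% | about 11 | 74.6% |
| 0.10 | 0.949 | 11% | about 22 | 77.0% |
| 0.20 | 0.894 | 25% | 50 | 82.1% |

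**Step 3. Re-hospitalization.** Section 2.2.3 cites 30% with standard care and 15% with music therapy. The planned model is a binary generalized linear mixed model with no link named; a logit link is assumed. For each scenario, 2,000 trials of 200 infants were simulated and analysed by logistic regression with and without a standardized covariate, at alpha 0.05. The odds ratio (OR) per SD of GA is an assumption.

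| OR per SD | Power, unadjusted to adjusted | SE of log OR | SE of risk difference (adjusted: standardized) |
|---|---|---|---|
| 1.0 | 72.8% to 73.0% | 0.362 to 0.363 | 0.0585 to 0.0587 |
| 1.5 | 73.7% to 74.2% | 0.361 to 0.369 | 0.0573 to 0.0567 (−1%) |
| 2.0 | 73.5% to 75.8% | 0.361 to 0.379 | 0.0579 to 0.0562 (−3%) |
| 2.5 | 74.2% to 77.8% | 0.362 to 0.392 | 0.0573 to 0.0535 (−7%) |

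The Monte Carlo SE of a single power figure is √(0.74 × 0.26 / 2000), about 1 point; both analyses use the same simulated trials. On the log-odds scale the SE rises, because the adjusted odds ratio lies further from 1. The gain shows up in power and in the standardized risk difference. The first row shows that adjusting for an irrelevant covariate costs almost nothing.

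**Step 4. Repeated outcomes.** Under the written model the group effect at a visit is β2 + β12 × time. With no pre-randomization score this is a between-infant contrast, which a GA main effect sharpens. If the effect is read from the time-by-group term alone, the participant term already absorbs stable differences between infants, and a GA-by-time term is needed for any useful gain. The assessment times for each instrument are in Figure 1, which is not available here, so which case applies cannot be settled.

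**The case against.** An unadjusted randomized analysis is valid, the outcomes are secondary, and the documents give no association between GA and any of them. At an R² of 2% the SE falls by only 1%. Assessments at 6 and 12 months are timed by corrected age, which already removes differences in age at testing, though not morbidity linked to immaturity. GA is also not overlooked, since it is a prespecified subgroup factor. All of this stands. It limits the size of the point but does not remove it, because a subgroup analysis does not adjust the main comparison.

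Four stronger readings are tempting and are not supported:

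- *GA is the main prognostic factor.* The documents do not rank prognostic factors. The fix needs only that GA be plausibly prognostic.
- *Chance imbalance biases the result.* With 200 analysed, a two-SE imbalance is 2 × √(4/200) = 0.28 SD of GA. At an assumed R² of 15% it shifts the estimate by 0.28 × √0.15 = 0.11 SD. That is 2 × √0.15 = 0.77 of the unadjusted SE of 0.141 SD, so it already lies inside the confidence interval. It is neither bias nor a second loss on top of the lost precision.
- *The percentage gains for continuous outcomes carry over to re-hospitalization.* They do not; see step 3.
- *A GA main effect is enough for every outcome.* It is not if an outcome is repeated and the effect is read from the time-by-group terms.

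**Conclusion.** The point holds as a matter of efficiency. The models applied to the infant outcomes contain no baseline covariate, although GA is recorded for everyone before the first randomization. Validity and type I error are not in question, and neither the primary PBQ analysis nor its sample size is touched.

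For a continuous outcome measured once, the gain runs from negligible to material across the assumed R² range of 2% to 20%; the documents do not allow it to be narrowed. For re-hospitalization it is small under the assumed odds ratios, with no reduction in the SE of the log odds ratio. For repeated outcomes it depends on a schedule that could not be seen. Because the change is close to free, it is worth making even at the low end.

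**What to change.** Add to section 2.2.4, before any unblinded analysis:

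- Models for BSID, ADBB and ASQ:SE include GA at birth (continuous, in weeks) as a fixed covariate, for both randomizations, with a GA-by-time term where the outcome is measured more than once.
- The logistic model for re-hospitalization includes the same covariate, and the result is reported as a standardized difference in proportions, the scale on which the power statement is expressed.

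The cost is a sentence or so of analysis wording. No new data are needed, because GA is already held for eligibility and subgroups. Pre-specification matters: adjustment added after an imbalance has been seen would look selective.

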### **2.2.2 Interventions**

The MT approach in this study is informed by models previously described and tested [18, 21, 25, 26]. Like other MT models [26], it is based on the notion that infants have a capacity to communicate actively [27, 28]. As in some newer models, parents are actively involved and empowered [21, 29]. The approach here thus builds on an emerging consensus, but is more explicit in its adaption to developmental levels and emphasis on infant/parent co-regulation. Furthermore, unlike previous studies [25], MT is extended beyond the tertiary care setting to help with the transition to daily life and municipal care. MT focuses on supporting positive relationship formation within the infant/parent dyad by promoting beneficial co-regulation, and includes psychosocial support of the parent.

**MT during NICU:** Participants will be offered individual MT sessions 3 times/week for 20-30 minutes/session, with a maximum of 36 sessions per infant (assuming a maximum NICU stay of 9 weeks). NICU-MT will be provided for all eligible infants once they achieve medical stability, usually after 26 weeks postmenstrual age (PMA; defined as GA at birth plus the time since birth [30]). A flexible protocol of procedures matched to infant PMA, familial/cultural preferences, and infant's demonstrated readiness to receive stimulation, will occur as individually-tailored sessions at bedside:

*Approximately 26 to 31.99 weeks PMA – Cautious use of sung/toned voice:* The music therapist shows caregivers how to use facilitated tucking and midline alignment (if appropriate for the infant) along with

[figure not shown]

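### The supplementary per-protocol analysis filters only the music therapy arm on sessions received, so it is not a randomized comparison; a complier-average estimate would serve better.

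*Combined protocol and SAP*

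**What the plan says.** Section 2.2.4 (Data analyses) makes intention-to-treat the main analysis, and section 2.3 confirms that the primary outcome is analysed irrespective of compliance. As a supplement, section 2.2.4 adds: "Per-protocol analyses will include those who received at least 6 MT sessions in the NICU and at least 5 MT sessions post-discharge, respectively". The reason given is: "these are considered the minimum numbers for the intervention to be successful". I read the two thresholds as defining one set per factor. No criterion for standard-care participants, no expected set size and no test level is attached to either set.

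The passages that determine who can reach the thresholds are these:

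- NICU schedule (section 2.2.2): "Participants will be offered individual MT sessions 3 times/week for 20-30 minutes/session".
- NICU start (section 2.2.2): "NICU-MT will be provided for all eligible infants once they achieve medical stability".
- NICU attendance (section 2.2.1): "Primary caregivers should agree to engage in at least 2 of the 3 MT sessions per week during NICU".
- Infant eligibility (section 2.2.1): "Born below 35 weeks GA, of both genders, any ethnicity, from single or multiple pregnancies", once stable enough to start. No minimum remaining stay is required. The listed amendments add criteria on parental language and capacity, not on stay.
- Post-discharge (sections 2.2.1 and 2.2.2): five to seven sessions over six months, of which caregivers agree to attend five.

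**The concern.** A standard-care family has no session count to fail. If the threshold is applied to MT families and all controls are kept, the two arms no longer come from the same population.

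In the NICU phase the threshold also mixes two things: whether the family took up what was offered, and whether the infant was in the unit long enough to be offered six sessions. A family that attends every session and goes home after ten days counts as off protocol, which is lack of opportunity and not non-adherence.

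The background (section 2.1) gives reason to think that the filter is related to the outcome. It links long hospitalization to difficulties in bonding, and it names maternal well-being or depression as leading influences on the relationship with the infant. It also says that MT may shorten hospital stay, so treatment could affect who passes the filter.

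At stake is how the supplementary result is read. Because the plan presents six and five as the minimum for success, a per-protocol difference could be taken as the effect of an adequate dose, particularly if the intention-to-treat result is null.

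**Working it through.** **1. Reference figures.** The plan gives no figure for the per-protocol set. Its power paragraph (section 2.2.4) supplies the scale: a target difference of 4 PBQ points, SD 8 and a two-sided 2.5% level per main effect. These reproduce the stated sample size. The normal formula gives 2 x [8 x (2.2414 + 0.8416) / 4]^2 = 76.04 per arm. The t-based solution gives 77.31 per arm, or 154.6 in total, which rounds up to the stated 155.

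**2. Who is in the set.** Taken literally, a set of participants who received at least six (or five) MT sessions contains no controls, and nothing can be compared. The workable reading keeps the controls and filters the MT arm. This is an inference, because the plan does not say it.

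**3. Time needed for six NICU sessions.** At the offered rate, 6 / 3 = 2 weeks from the start of MT. This is approximate: with three sessions a week, the sixth can fall on about day 12. At two a week it would be 6 / 2 = 3 weeks, but that applies only if sessions lapse when the caregiver is absent, which the documents do not say.

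Separately, section 2.2.2 sets the NICU course "with a maximum of 36 sessions per infant (assuming a maximum NICU stay of 9 weeks". At three a week, 36 sessions take 36 / 3 = 12 weeks, while 9 weeks give 9 x 3 = 27. Those figures must be reconciled, but nothing here depends on them.

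**4. Spurious difference with no treatment effect.** Let f be the share of the MT arm excluded, and g the gap in mean PBQ change between families who would be excluded and those who would be retained. The retained MT mean is m. The control mean is (1 - f) x m + f x (m + g) = m + f x g. The arms therefore differ by f x g in size although treatment does nothing. The documents give neither f nor g, so the values below are assumptions.

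The error rates come from a simulation with 100 per arm (about half of the plan's 203), SD 8, no treatment effect, stay unaffected by allocation, and 20,000 runs per row.

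| f | g (points) | f x g (points) | Share of 4-point target | Type I error (nominal 2.5%) |
|---|---|---|---|---|
| 10-40% | 0 | 0 | 0% | 2.4-2.5% |
| 10% | 2 | 0.2 | 5% | 2.6% |
| 20% | 2 | 0.4 | 10% | 3.1% |
| 20% | 4 | 0.8 | 20% | 5.8% |
| 30% | 4 | 1.2 | 30% | 10.0% |
| 40% | 2 | 0.8 | 20% | 5.2% |
| 40% | 4 | 1.6 | 40% | 15.4% |

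When the same kind of infant is removed from both arms, the bias is about 0 and the error rate is 2.2% to 2.6%. The asymmetry causes the distortion, not the loss of numbers.

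**The case against.** The strongest reply is that this is a supplementary analysis. The main analysis is intention-to-treat, no power or conclusion rests on the per-protocol set, and its misreading is a prediction. That stands, and it limits the point to an improvement of a secondary analysis.

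The post-discharge threshold is also more defensible than the NICU one. Five sessions is the programme's own minimum and what caregivers agree to, so failing it is ordinary non-adherence and not lack of opportunity. That stands too. What remains is that attendance is still selected in one arm only.

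Four stronger readings are tempting, and the documents do not support them:

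- A reader might infer that length of stay sets the NICU count. It only caps it; attendance and the time of reaching stability matter as well.
- A reader might infer that the excluded infants are mainly the mature, healthy ones, so that the direction of bias is known. Infants who stabilize late or whose sessions are interrupted can also miss six sessions. The endpoint is change in PBQ, and the documents say nothing about how change differs by stay.
- A reader might take the plan's words on minimum numbers as showing that fewer sessions do nothing. They express a view about adequate dose. Caregivers are taught techniques that they can use on their own (section 2.2.2), so partial exposure may have an effect.
- A reader might take 1.6 points as an estimate. It is the top of an assumed range, and a 4-point gap is as large as the trial's whole target difference.

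**Conclusion.** The point holds for the supplementary per-protocol analysis. As written, the set has no defined control side. On the workable reading it removes participants from the MT arm only, partly for lack of opportunity in the NICU phase and by attendance after discharge, so randomization does not protect the comparison.

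The size cannot be determined from the documents. It is zero if excluded and retained families do not differ in PBQ change, and reaches about 1.6 points, or 40% of the target difference, if 40% are excluded and the gap is 4 points. The direction is unknown. The conclusion rests on the inference that all controls are kept; if the sponsor intended another control rule, it needs to be stated. The intention-to-treat result and the sample size are not touched.

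**What to change.** For each factor, make the supplementary adherence analysis a complier-average causal effect, estimated by instrumental variables in all participants randomized at that step. The first allocation is the instrument for receiving at least six NICU sessions, and the second for at least five post-discharge sessions. Adjust for baseline PBQ, gestational age at birth and country.

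State the exclusion restriction openly as an assumption: allocation affects PBQ only through reaching the threshold. Because sessions below the threshold may have some effect, and would then inflate the estimate, add a sensitivity version that defines receipt as any session or as the number of sessions.

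If a per-protocol table is kept, state which controls it includes, adjust it for the same baseline variables and label it descriptive. Applying a common length-of-stay rule to both arms would be weaker, because stay is observed after randomization and section 2.1 says that MT may shorten it.

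The cost is SAP wording and one model per factor plus its sensitivity version, using data already planned. The downsides are reliance on the exclusion restriction and wider intervals. In the simplest form the estimate is the intention-to-treat difference divided by the share of the MT arm reaching the threshold, so its interval is roughly 1 / 0.8 = 1.25 times as wide if 20% fall short and 1 / 0.6 = 1.67 times if 40% do (both shares assumed).
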